### Sample size

2.5

The VAS score is the primary outcome measure of this trial. Based on the preliminary results from the research team’s earlier trials, the estimated VAS score for the treatment group after intervention is 1.6 ± 1 cm. Based on the data from relevant domestic clinical trials (26) and our preliminary exploratory trials, we predict that the VAS score for the control group is 2.41 ± 1.68 cm. The sample size ratio for the two groups is 1:1. Using PASS15 to calculate the sample size, with a two-sided test set at *α* = 0.05 and *β* = 0.10, and a test power of 0.9, at least 41 participants are needed in each group. Considering a 15% dropout rate, a total of 48 participants will need to be recruited for each group, resulting in a total of 96 participants required.

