#### Secondary outcome

2.8.2

Nylon Filament Test (10 g Monofilament Test): A 10 g monofilament is used to stroke the skin area where the patient feels numb. The numb skin area is stroked 10 times, and the number of strokes perceived is observed and recorded. Perceiving 7–10 strokes is considered normal, 1–6 strokes is considered reduced sensation, and 0 strokes is considered absent sensation. The researcher records these as 3 points, 2 points, and 1 point, respectively. The study indicates that tactile static testing using a 10 g monofilament demonstrates the highest sensitivity for detecting superficial sensory disturbances. It can be recommended as the most sensitive single testing tool (28).

Pinprick Test (40 g Pressure Pinprick Test): A blunt-tipped pressure needle is used to apply a constant force to the patient’s numb area. The presence or absence of pain is observed and recorded, with pain scored as 1 point and no pain scored as 0 points. The experiment differentiates neuropathic pain from sensory loss by assessing Aδ fiber function, with sensitivity and specificity ranging from 68 to 85% and 79 to 92%, respectively (29). The test demonstrates good reproducibility (ICC = 0.89) in the assessment of postoperative neuropathy (30).

Other secondary indicators: JOA (Japanese Orthopedic Association) Score, a study mentioned that the JOA scoring system was used to evaluate 89 patients who underwent lumbar decompression surgery, and it was found that 30.3% of patients still had mild lower extremity pain/numbness and 14.6% of patients still had gait disturbances 2 years after the surgery. This indicates that the JOA scoring system can effectively identify residual symptoms after surgery (31). Traditional Chinese Medicine Syndrome Score, the TCM Syndrome Score does not focus solely on individual symptoms, but rather considers multiple symptoms and signs comprehensively, providing a more holistic assessment of the patient’s condition, it has high effectiveness in evaluating treatment outcomes (32). Additionally, Lower Limb Electromyography (H-reflex difference, F-wave conduction velocity, and latency), VAS Score, SF-36 (Short Form 36 Health Survey Questionnaire). The evaluation time points are detailed in Table 1.

**Table 1 tab1:** Timeline for the collection of evaluation indicators.

Observation indicators	Pretreatment	Treatment stage		Follow-up phase	
	Baseline (in geodetic survey)	1 week	4 weeks	12 weeks after treatment	24 weeks after treatment

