### Statistical analysis

2.12

Sample size calculation was performed using PASS software (version 15.0, NCSS LLC). Based on preliminary data, the estimated mean (standard deviation) of the VAS numbness score after intervention for the treatment group (UA + WA) is 1.6 ± 1.0 cm, and for the control group (electroacupuncture) it is 2.41 ± 1.68 cm. To detect a between-group difference of 0.81 cm with 90% power (*β* = 0.10) and a two-sided *α* of 0.05, at least 41 participants are required in each group. Considering a 15% dropout rate, the final sample size is set at 48 participants per group (96 participants in total). This calculation complies with the CONSORT guidelines for randomized controlled trials.

All analyses will follow the intention-to-treat (ITT) principle, including all randomized participants. Additionally, for sensitivity analysis, a per-protocol set (PPS) analysis will be conducted, excluding participants with major protocol deviations (e.g., fewer than 8 acupuncture sessions, and use of prohibited medications). The primary outcome, the change in VAS numbness score over time points (baseline, 1 week, 4 weeks, 12 weeks, 24 weeks), will be assessed using a linear mixed-effects model (LMM). The model will include group, time, group-by-time interaction, and baseline VAS score as fixed effects. Random intercepts and slopes will account for within-individual variability. Missing data will be handled using multiple imputation (MI) with fully conditional specification (FCS) in SAS 9.4 (SAS Institute), generating 10 imputed datasets. Estimates will be combined according to Rubin’s rules. Sensitivity analysis will compare MI with the last observation carried forward (LOCF). For secondary outcomes with continuous variables (e.g., JOA, SF-36), the same LMM structure as the primary outcome will be used. For ordinal/categorical variables (e.g., TCM syndrome score), proportional odds logistic regression or generalized estimating equations (GEE) will be applied to longitudinal ordinal data. For binary outcomes (e.g., adverse events), comparisons between groups will be made using the chi-square test or Fisher’s exact test (for small sample sizes). Risk ratios (RR) and 95% confidence intervals (CI) will be reported.

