The success of assessor blinding will be evaluated using James’ blinding index. A value close to 0.5 indicates effective blinding (0 = completely unblinded; 1 = completely blinded). If there are baseline differences (e.g., age, baseline VAS score), adjustments will be made using analysis of covariance (ANCOVA). Pre-specified subgroups (e.g., age < 50 vs. ≥ 50 years, baseline VAS score severity) will be explored using interaction terms in regression models. *p*-values will be adjusted using the false discovery rate (FDR) correction for multiple comparisons for the primary outcome.

Adverse events (AE) will be graded according to CTCAE v5.0. The incidence rates between groups will be compared using the chi-square test (or Fisher’s exact test for rare events). Descriptive analysis will be conducted for serious adverse events (≥ grade 3). Analyses will be performed using SAS 9.4 (SAS Institute) and SPSS 26.0 (IBM Corp). Continuous outcomes will be reported as mean differences (MD) with 95% CI and effect sizes (Cohen’s d). Categorical outcomes will be reported as risk ratios (RR) with 95% CI. Exact *p*-values will be provided for all tests, with a significance level set at *p* < 0.05 for the primary outcome.

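### The primary mixed model, as written, uses baseline VAS as both a response visit and a covariate, so the group-by-time test gains nothing from the adjustment and standard errors at single visits are misstated

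*Protocol article*

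**What the plan says.** All of this is in the protocol article, mostly in section 2.12 (Statistical analysis).

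- The primary outcome is "the change in VAS numbness score over time points (baseline, 1 week, 4 weeks, 12 weeks, 24 weeks", so baseline is one of five outcome time points.
- Fixed effects: "The model will include group, time, group-by-time interaction, and baseline VAS score as fixed effects". Baseline VAS enters as a main effect only; no baseline-by-time term is named.
- Random effects: "Random intercepts and slopes will account for within-individual variability".
- A further, conditional adjustment is added: "If there are baseline differences (e.g., age, baseline VAS score), adjustments will be made using analysis of covariance (ANCOVA". It does not say how it relates to the mixed model, which already contains baseline VAS.
- Continuous secondary outcomes, such as JOA and SF-36, reuse the primary model's structure.
- No contrast (the interaction, or the group difference at a given visit) is named as the primary test.

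Table 1 in section 2.8.2 labels the first follow-up visit "12 weeks after treatment" and the second correspondingly at 24 weeks. Section 2.12 lists them simply as 12 and 24 weeks.

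**The concern.** If baseline VAS is a response row and also a covariate, then at the baseline visit the covariate equals the response. Taking the outcome as change from baseline does not help: the baseline row is then exactly 0 for everyone, and the model is the same one with the baseline coefficient shifted by 1. Only leaving out that row removes the problem, and the text does not say that it is left out.

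Two consequences need separate treatment because they affect different tests. A covariate that is constant within a patient drops out of a comparison of that patient's visits, so the group-by-time test gains nothing from it. And the variance model is fitted partly to a row that the covariate explains almost perfectly, which can distort the standard error of an adjusted group difference at a single visit. Week 4 matters most here. Section 2.1 makes it the end of the intervention period, and the sample size is built on the score after intervention, so a week-4 difference is a natural headline result.

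**Working it through.** **Inputs from the documents.** Section 2.5: "the estimated VAS score for the treatment group after intervention is 1.6 ± 1 cm" and "we predict that the VAS score for the control group is 2.41 ± 1.68 cm". Section 2.12: difference 0.81 cm, two-sided 5%, 90% power, 41 per group before and 48 after dropout.

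**Assumptions, not in the documents.** Baseline-to-follow-up correlation ρ, covariance between visits, and baseline SD equal to follow-up SD unless stated.

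**The plan's own figure.** n per group = (1.960 + 1.282)² × (1.0² + 1.68²) / 0.81² = 10.51 × 3.822 / 0.656 = 61.2, so 62. The stated 41 does not come out; power at 41 is 75.6%. That is a separate matter. Only the SDs and the difference are carried forward.

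**Step 1: the covariate cancels.** Write the mean of patient i at visit t as a_t + g_t × group_i + β × baseline_i. Visit t minus the baseline visit is (a_t − a_0) + (g_t − g_0) × group_i, and β × baseline_i has gone. With complete or imputed data and categorical time, the interaction estimate is therefore the difference in mean change. In one simulated trial with a random intercept, the week-4 interaction was 0.3281 (SE 0.2545) both with and without the covariate. With a random slope added, the estimate was again unchanged and the SE nearly so (0.2516 against 0.2544).

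**Step 2: what that costs.** Common SD = √((1.0² + 1.68²)/2) = 1.382.

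- Change score: SE = 1.382 × √(2(1 − ρ)) × √(2/n)
- Baseline-adjusted: SE = 1.382 × √(1 − ρ²) × √(2/n)
- Power = Φ(0.81/SE − 1.96)

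| n per arm | ρ | change SE | power | adjusted SE | power |
|---|---|---|---|---|---|
| 48 | 0.3 | 0.334 | 67.9% | 0.269 | 85.3% |
| 48 | 0.5 | 0.282 | 81.9% | 0.244 | 91.2% |
| 48 | 0.7 | 0.219 | 96.0% | 0.202 | 98.0% |
| 41 | 0.3 | 0.361 | 61.1% | 0.291 | 79.4% |
| 41 | 0.5 | 0.305 | 75.6% | 0.264 | 86.5% |
| 41 | 0.7 | 0.237 | 92.9% | 0.218 | 96.0% |

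With a smaller baseline SD (1.2 against 1.38 at follow-up), the change-score SE is still about 16% larger at ρ = 0.3 (1.533/1.316) and 9% larger at ρ = 0.5 (1.299/1.195).

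**Step 3: standard errors, checked by null simulation.** The main run had 48 per arm, five visits, 1,000 trials per cell and four covariance patterns: compound symmetry, AR(1), small-variance baseline and a true random slope. Models had categorical time and, as the plan states, a random intercept and slope. Monte Carlo error is about 0.7 points at a 5% rate.

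| Group difference | Model/empirical SE | Type I error |
|---|---|---|
| Week 4, double use | 0.78 to 0.88 | 8.8% to 13.2% |
| Week 24, double use | 1.01 to 1.10 | 3.8% to 5.2% |
| Averaged over visits, double use | 0.99 to 1.01 | not inflated (5.3% to 5.4% in three patterns) |
| Single visits, post-baseline responses with baseline as covariate | 0.94 to 1.05 | |

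Two smaller simulations agree at week 4:

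- 41 per group, 300 runs per scenario: SE ratios 0.250/0.306, 0.225/0.250 and 0.253/0.315, that is 0.82, 0.90 and 0.80. Rejection was 8.7%, 9.7% and 10.0%, against 3.7% to 5.0% for a week-4 ANCOVA.
- 48 per arm, 120 runs: 0.218/0.251 = 0.87, with about 11% rejection. Dropping the baseline row gave 0.257/0.250 = 1.03 and 5%.

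**Step 4: is double use the cause for the interaction?** The joint group-by-time test had type I error of 5.2% to 6.6% across all patterns. Some single interaction contrasts had SEs that were too small (ratio 0.80 to 0.83 under AR(1), 0.89 to 0.96 with a small-variance baseline). They were about as small with the covariate removed (0.80 to 0.93), so misfit of the covariance explains them.

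**Step 5: time axis.** With 4 weeks of treatment, Table 1 puts the follow-up visits at about 4 + 12 = 16 and 4 + 24 = 28 weeks from baseline.

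**The case against.** **Double use is only one reading.** A change needs baseline as its reference, and the list of time points matches the Table 1 schedule. If change is computed at the four later visits with baseline as covariate, the model is standard, and a condensed article may leave the choice of rows to the analysis plan. This stands in part: the text never says outright that baseline rows are responses. But it lists baseline among the outcome time points, adds it as a covariate in the next sentence, and excludes nothing. An analyst who follows the stated model gets the weaker analysis.

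**A change-score test is valid.** This stands. Under randomisation it is unbiased, so the loss is precision, and at a correlation of 0.7 the loss is small.

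**Cancellation is not specific to double use.** This also stands. A baseline main effect drops out of contrasts between visits even when only post-baseline rows are used. The remedy must therefore change the contrast tested as well as the rows.

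**The stronger reading.** A reader might infer that the model's standard errors are too small throughout, and that the primary type I error therefore exceeds 5%. The documents do not support this. They name no primary contrast, the joint interaction test stayed near its nominal level, week-24 and visit-averaged standard errors were correct or conservative, and the small interaction SEs come mainly from covariance misfit.

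**The time-axis difference is probably shorthand.** Sections 2.1 and 2.12 can be read together with Table 1, and the coding of slope time is not stated. It is a secondary point that matters only if a random slope is kept.

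**Conclusion.** The concern holds in limited form. As written, baseline VAS is both a response visit and a main-effect covariate in the primary model.

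- For group-by-time contrasts against baseline, the covariate does nothing. The test is an unadjusted change-score comparison. At 48 per arm it gives up about 17 points of power at ρ = 0.3, 9 at 0.5 and 2 at 0.7.
- For adjusted differences at single visits, the standard error is misstated in a direction that depends on visit and covariance: too small at week 4 (ratio about 0.78 to 0.90, type I error about 9% to 13%), correct or too large at week 24.

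The first result is algebra, exact for complete or imputed data with categorical time. Its size rests on an assumed correlation, equal baseline and follow-up SDs, and all n patients contributing. The second rests on assumed covariances and a random intercept and slope. Neither shows that the primary result would be invalid in general.

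**What to change.** Reword the model in section 2.12, for the primary outcome and for the continuous secondary outcomes that reuse it:

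1. Use only post-baseline VAS as responses: 1 week, 4 weeks, and 12 and 24 weeks after treatment. State that baseline is not a response row.
2. Keep baseline VAS as a covariate and add baseline-by-visit.
3. Make the primary test the group difference at a named visit, for example week 4, the end of treatment.
4. If a random slope is kept, code time as actual weeks since baseline (about 1, 4, 16 and 28). Categorical visits with an unstructured within-patient covariance are a reasonable alternative but are not needed to cure the double use.

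One practical exception concerns electromyography. Table 1 measures it only at baseline, 1 week and 4 weeks, which leaves two post-baseline visits. Two visits supply three variance-covariance terms, while a random intercept and slope with residual needs four, so the random slope has to go there.

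The cost is analysis wording only. Section 2.14 says enrolment has begun, so the change should be a dated amendment made before database lock and before any comparison by group.

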### Design

2.1

This study is a prospective, assessor-blinded, randomized controlled trial. A total of 96 participants will be recruited at the Zhejiang Provincial Hospital of Traditional Chinese Medicine. Participants will be randomly assigned to either the experimental group or the control group in a 1: 1 ratio. The trial will consist of a 4-week intervention period followed by a 6-month follow-up period. The flowchart of the research procedure is shown in Figure 1. This study will be designed and reported by the Declaration of Helsinki, the Consolidated Standards of Reporting Trials (CONSORT) (24), and the Standards for Reporting Interventions in Controlled Trials of Acupuncture (STRICTA) guidelines (25). Any potential modifications to the protocol that may affect the conduct of the study will be formally documented as amendments. Before such updates are implemented, they will be decided by the project management team and approved by the ethics committee. The trial has been registered with the Chinese Clinical Trial Registry, number ITMCTR2024000328.

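### Ten imputed datasets are enough for the estimate but leave avoidable simulation noise in a primary p-value near 0.05; at least 100 would remove most of it (minor)

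*Protocol article*

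**What the plan says.** Section 2.12 of the protocol article fixes the imputation in some detail: fully conditional specification "in SAS 9.4 (SAS Institute), generating 10 imputed datasets", and then "Estimates will be combined according to Rubin’s rules". The primary outcome is the numbness VAS score, analysed by a linear mixed model over baseline and weeks 1, 4, 12 and 24. For reporting, the same section promises that exact "values will be provided for all tests, with a significance level set at" p < 0.05 for the primary outcome. It also applies a false discovery rate correction to multiple comparisons on that outcome.

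Section 2.5 gives the test as a "two-sided test set at *α* = 0.05". The expected loss appears in 2.5 and again in 2.12: "Considering a 15% dropout rate, the final sample size is set at 48 participants per group", which makes 96 in total. The article states no FMI, no timing of dropout and no criterion for simulation error.

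**The concern.** Multiple imputation draws random values. Each seed therefore gives a slightly different pooled estimate and pooled standard error from the same trial data. The usual argument for a small number of imputations, M, concerns the efficiency of the estimate, and M = 10 passes that test. A p-value set against a threshold needs more, because small shifts in the test statistic near 0.05 can move it across the line. If the true answer is borderline, the superiority verdict could partly reflect an arbitrary seed. Since the article itself fixes M, the choice can be assessed here without the SAP.

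**Working it through.** **Plan's own figure.** The article gives no figure for simulation error, so there is none to reproduce.

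**Inputs from the article.** M = 10 (2.12); 15% dropout, which is 0.15 × 48 = 7.2, about 7 per arm (2.5, 2.12); 48 per arm (2.5); two-sided alpha 0.05 (2.5); VAS 1.6 (SD 1.0) against 2.41 (SD 1.68), difference 0.81 cm (2.5, 2.12).

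**Assumptions.** FMI f between 0.06 and 0.15; complete-data degrees of freedom 96 − 3 = 93 (two groups, adjusted for baseline); one unadjusted contrast.

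**Step 1: is the FMI range reasonable?** Trials were simulated with 48 per arm, five visits, 7 dropouts per arm and several visit correlations.
- All losses before week 1: FMI about 0.15 to 0.17.
- Losses spread over visits, week-24 contrast: about 0.13 to 0.16.
- Losses spread over visits, week-4 contrast or average over visits: about 0.06 to 0.10.

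**Step 2: the estimate.** Finite M multiplies the variance by about 1 + f/M. That is 1 + 0.15/10 = 1.015 at f = 0.15 and 1 + 0.06/10 = 1.006 at f = 0.06. There is no bias.

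**Step 3: quick check on the test statistic.** Given the data, the pooled estimate varies over seeds with SD of about sqrt(f/M) standard errors. At f = 0.15 and M = 10 this is sqrt(0.015) = 0.122. A statistic of 1.96 then ranges over 1.96 ± 1.96 × 0.122, or 1.72 to 2.20, which is p from 0.085 to 0.028.

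**Step 4: full calculation.** Step 3 ignores noise in the between-imputation variance, which rests on M − 1 = 9 degrees of freedom. Let B be the between-imputation variance and W the within-imputation variance, with f = B/(W + B). Draw the pooled estimate from N(Q, B/M) and the estimated between variance as B × chi-square(M − 1)/(M − 1). Set T = W + (1 + 1/M) × (estimated between variance) and use Barnard-Rubin degrees of freedom. Choose Q so that the p-value with unlimited imputations is 0.05. Central 95% range of the reported p-value, 400,000 draws:

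| FMI | M = 10 | M = 100 |
|---|---|---|
| 0.06 | 0.035–0.073 | 0.045–0.056 |
| 0.08 | 0.033–0.078 | 0.044–0.057 |
| 0.10 | 0.031–0.083 | 0.043–0.058 |
| 0.15 | 0.027–0.095 | 0.041–0.061 |

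**Step 5: how close to 0.05 must a result be?** Share of seeds giving the opposite verdict at f = 0.15:

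| p with unlimited imputations | M = 10 | M = 100 |
|---|---|---|
| 0.03 | 9% | 0% |
| 0.04 | 30% | under 2% |
| 0.06 | 24% | 3% |
| 0.07 | 12% | 0.02% |

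At f = 0.06 and M = 10 the shares are about 1%, 14%, 14% and 3%.

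**Step 6: how often are results that close?** With 48 per arm, SE = sqrt((1.0² + 1.68²)/48) = sqrt(3.8224/48) = 0.282, so the expected statistic is 0.81/0.282 = 2.87. The limits p = 0.03 and p = 0.07 correspond to 2.170 and 1.812. The probability between them is Φ(2.170 − 2.870) − Φ(1.812 − 2.870) = 0.242 − 0.145 = 0.097. With 41 per arm the statistic is 0.81/0.305 = 2.65 and the probability is 0.114. So about 10% of trials are borderline in this sense.

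**Step 7: overall disagreement.** Averaging over trials on these inputs, share in which one run disagrees with the unlimited-imputation verdict:

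| Per arm | FMI | M = 10 | M = 100 |
|---|---|---|---|
| 48 | 0.06 | 1.8% | 0.6% |
| 48 | 0.10 | 2.5% | 0.8% |
| 48 | 0.15 | 3.3% | just under 1% |
| 41 | 0.06 | 2.2% | 0.7% |
| 41 | 0.10 | 2.9% | 0.9% |
| 41 | 0.15 | 3.9% | 1.2% |

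**The case against.** The strongest reply is that the plan contains no error here. M = 10 is adequate for the estimate, every finite M leaves some dependence on the seed, and a seed fixed in advance makes the reported number repeatable and prevents choosing among results. All of that stands. The seed is normally set in the SAP, which is not shown, so its absence from the article is not a fault. What remains is the size of the noise. A fixed seed makes a p-value repeatable, but a verdict near the threshold still rests on an arbitrary number, and a larger M removes most of that.

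Three stronger readings are tempting, and the article does not support them.
- **That 15% dropout means an FMI of 0.15.** The article gives no FMI. Participants who leave late still contribute earlier visits to the mixed model, and the planning means are described as post-intervention values, which may point to week 4 rather than week 24. In that case 0.06 to 0.10 is plausible.
- **That a borderline result could land anywhere from about 0.02 to 0.09.** For a p-value of 0.05 with unlimited imputations, the lower limit is 0.027 even at FMI 0.15.
- **That borderline results are likely because power is low.** On the article's means and SDs, power is about 76% with 41 per arm and 82% with 48, not 90%. This is a separate and more serious matter. It hardly changes the present point: the chance of p between 0.03 and 0.07 is about 10 to 11%, against about 7% at a true 90% power.

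The calculation also treats one unadjusted contrast at 0.05, whereas 2.12 adjusts multiple comparisons on the primary outcome. The noise would then act around the adjusted threshold, so the percentages are indicative.

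**Conclusion.** The point holds as a minor one. Fixing M at 10 leaves avoidable simulation noise in the exact primary p-value, while the estimate is essentially untouched. Clear results in either direction are safe; the exposure is confined to results already near the threshold. Moving to M = 100 lowers overall disagreement by roughly 1 to 3 percentage points. The direction holds at every FMI examined. The size depends on the assumed FMI, on the article's planning means and SDs, and on the single-contrast simplification.

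**What to change.** In section 2.12, replace "generating 10 imputed datasets" with a statement that at least 100 imputed datasets will be generated, and apply the same number to the secondary outcomes. The seed can be recorded in the SAP. With 96 participants and five visits the only cost is a little computing time; no participants, visits or staff are added, and nothing else in the design changes.

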#### Inclusion criteria

2.3.1

(1) Age range from 22 to 60 years old; (2) Patients with lumbar disc herniation who underwent PELD surgery and were assessed to have residual numbness symptoms on the first day after surgery; and (3) Numbness with a VAS score greater than 40 mm (score ≥ 40 mm on a 100 mm Visual Analog Scale [VAS]).

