According to domestic literature reports, electroacupuncture has a definite therapeutic effect in treating residual pain and numbness after percutaneous transforaminal endoscopic discectomy (PTED) for LDH. The overall effective rates for pain and numbness relief are 95.45 and 92.86%. The overall efficacy of combined electroacupuncture treatment is superior to that of Western medicine treatment alone (37). Some other articles have reported that low-frequency EA was applied directly to the spinal nerve root at right L4, L5, and, S1, immediately after treatment, right or left back and lower extremity pain and numbness were markedly reduced. The walking distance of patients was also greatly extended. The mechanisms underlying this effect may be attributed to inhibitory control at the spinal level, inhibition of potential activity by hyperpolarization of nerve endings, or changes in nerve blood flow (38, 39).

Therefore, we have established an electroacupuncture control group. We will compare this treatment with electroacupuncture therapy to explore a potentially more effective acupuncture treatment regimen that promotes early rehabilitation for patients with numbness after LDH surgery. We hope to find a better acupuncture treatment method to guide clinical practice and improve treatment outcomes. In addition, this study may provide more scientific evidence for non-pharmacological treatments and facilitate future related research.

This study has certain limitations. Its single-center design may not fully represent the clinical practice situation across multiple centers. The VAS (Visual Analog Scale) score is a subjective outcome measure that is susceptible to individual differences and psychological factors among patients. The follow-up period of this study is 6 months, which may not be sufficient to fully assess the long-term effects of the treatment. Insufficient sample size may affect the statistical power of the results, and there may be issues with poor patient compliance and high dropout rates in the study.

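### LOCF, the one missing-data sensitivity analysis named, assumes no change after dropout, which the plan's own figures contradict, and cannot show how far missing-at-random may fail

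*Protocol article*

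**What the plan says.** All of the following is from the protocol article.

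- Primary model (2.12 Statistical analysis): the numbness VAS at baseline and 1, 4, 12 and 24 weeks "will be assessed using a linear mixed-effects model (LMM").
- Missing data (2.12): "Missing data will be handled using multiple imputation (MI) with fully conditional specification (FCS) in SAS 9.4", with 10 imputed datasets pooled by Rubin's rules.
- Check on the missing data (2.12): "Sensitivity analysis will compare MI with the last observation carried forward (LOCF").
- Other sensitivity analysis (2.12): "for sensitivity analysis, a per-protocol set (PPS) analysis will be conducted, excluding participants with major protocol deviations". This changes who is analysed, not what is assumed about absent scores.
- Entry level (2.3.1 Inclusion criteria): "Numbness with a VAS score greater than 40 mm", restated in brackets there as 40 mm or above.
- Expected outcome (2.5 Sample size): "the estimated VAS score for the treatment group after intervention is 1.6 ± 1 cm"; the control arm is put at 2.41 cm with SD 1.68 cm.
- Dropout: the sample size is set "Considering a 15% dropout rate", and the limitations in the Discussion say that "there may be issues with poor patient compliance and high dropout rates in the study".

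**The concern.** A mixed model and standard fully conditional imputation both take the missing scores to be predictable from the observed ones (missing at random, MAR). A useful sensitivity analysis relaxes that by stages and shows where the conclusion gives way. LOCF instead swaps MAR for a single different assumption: no change after the last visit. The expected means imply a sizeable fall during treatment, so a score carried from early in treatment lies above what the plan itself expects.

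Its error can also go in either direction, depending on which arm loses more patients, so LOCF cannot be relied on as a conservative check. Agreement with MI could be taken as reassurance that it does not give, and disagreement could cast doubt on a sound result. The plan budgets for dropout and warns that it may be high, so this check is likely to be called on.

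**Working it through.** **Inputs from the document.** Expected post-treatment means 1.6 cm (UA + WA) and 2.41 cm (electroacupuncture); SDs 1.0 and 1.68 cm; dropout 15%; 48 per group; entry at about 4 cm or more.

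**Assumptions, not in the document.** Common baseline mean B of 4 to 6 cm (only the entry floor is given). Dropouts would have reached their arm's mean. For unequal dropout, a 10%/20% split, which keeps the planned 15% overall.

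**Step 1, the plan's difference.** 2.41 − 1.6 = 0.81 cm, as section 2.12 states.

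**Step 2, the implied fall.** From 4 cm: 4 − 1.6 = 2.4 cm (60%) and 4 − 2.41 = 1.59 cm (40%). A higher baseline mean makes both larger.

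**Step 3, LOCF with baseline carried.** Arm mean = (1 − q) × expected mean + q × carried score, where q is the dropout proportion.

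- 15% in each arm: B cancels, leaving 0.85 × 0.81 = 0.69 cm.
- 20% treatment, 10% control: (0.9 × 2.41 + 0.1B) − (0.8 × 1.6 + 0.2B) = 0.889 − 0.1B, which is 0.49 cm at B = 4 and 0.29 cm at B = 6.
- 10% treatment, 20% control: (0.8 × 2.41 + 0.2B) − (0.9 × 1.6 + 0.1B) = 0.488 + 0.1B, which is 0.89 cm at B = 4 and 1.09 cm at B = 6.

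**Step 4, half the fall already achieved at dropout.** The carried score is (B + arm mean)/2.

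| Dropout, treatment / control | Baseline carried | Half the fall achieved |
|---|---|---|
| 15% / 15% | 0.69 cm (−15%) | 0.75 cm (about −7%) |
| 20% / 10% | 0.49 to 0.29 cm (−40% to −64%) | 0.65 to 0.55 cm (−20% to −32%) |
| 10% / 20% | 0.89 to 1.09 cm (+10% to +34%) | 0.85 to 0.95 cm (+5% to +17%) |

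Ranges run from B = 4 to B = 6; percentages are relative to 0.81 cm.

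**Step 5, no true effect.** With both arms at 2.41 cm, 10% treatment and 20% control dropout and baseline carried, LOCF gives 0.10 × (B − 2.41) = 0.16 to 0.36 cm in favour of UA + WA.

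**Step 6, standard error.** Take 15% dropout per arm and carried scores that lie 2 cm higher with the same SD. Mixing adds 0.15 × 0.85 × 2² = 0.51 to each variance. LOCF: √[(1.51 + 3.33)/48] = 0.318 cm. Completers (0.85 × 48 ≈ 41 per arm): √[(1.00 + 2.82)/41] = 0.305 cm. With a 1 cm gap the LOCF figure is 0.291 cm. LOCF ignores imputation uncertainty, but its standard error may come out larger or smaller.

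**Step 7, what a delta analysis would show.** Adding δ to the imputed 15% of the UA + WA arm alone reduces the difference by 0.15δ. If 0.81 cm were observed, a simple two-sample comparison would reach z = 1.96 at δ = (0.81 − 1.96 × 0.305)/0.15 = 1.41 cm. With the standard error for 48 per arm, √(3.82/48) = 0.282 cm, it would do so at 1.71 cm. A range of 0.5 to 2.0 cm would therefore bracket the turning point in this example.

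**The case against.** The strongest reply is that LOCF is only a sensitivity analysis. A reader might infer that it biases the trial's result or could overturn it. The document does not support that: the result comes from the mixed model with MI, and nothing in section 2.12 lets LOCF override it. This stands in full.

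Second, no improvement after leaving is itself a departure from MAR, and for patients who leave because they are not improving, a carried score may be roughly right. It would be too strong to say that the comparison tells us nothing about informative dropout. What it offers is one ungraded departure, not a scale of them.

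Third, the article gives no baseline mean, week-1 score or trajectory, and its Introduction says that numbness recovers more slowly than pain. A steep early fall is therefore an inference from the entry floor and the expected means. Dropout after week 4 carries a week-4 score, and no later change is forecast; if scores plateau, the error there is small. The 10%/20% split is likewise assumed. Nor should one assert that patients know their treatment: sections 2.1 and the Abstract describe assessor-blinded or single-blind conduct, whereas the Discussion says patients are blinded too.

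Fourth, a reader might infer that LOCF always understates the standard error. Step 6 shows otherwise.

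Finally, an unseen analysis plan may contain further checks. The point is therefore not that something is absent but that the article positively selects an unsuitable method.

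**Conclusion.** The point holds as a weakness in the robustness check, not in the primary analysis. For dropout during treatment, LOCF imposes an assumption at odds with the plan's own entry level and expected means. Under the stated assumptions it moves the 0.81 cm difference to 0.69 cm with equal 15% dropout, and to anywhere between 0.29 and 1.09 cm with a 10%/20% imbalance. The direction depends on which arm loses more patients. These figures illustrate rather than predict: they rest on an assumed baseline mean of 4 to 6 cm, baseline being carried, and dropouts otherwise reaching their arm's mean. They roughly halve if half the fall precedes dropout. The change is worth making, but the trial does not stand or fall by it.

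**What to change.** Replace LOCF, or keep it only as a supplementary analysis, with delta-adjusted multiple imputation in the SAS 9.4 software already planned. Prespecify a range of deltas, for example 0.5 to 2.0 cm (an assumed range, to be justified clinically), and add them to the imputed numbness scores in the UA + WA arm alone and then in both arms. Report the delta at which the primary group comparison changes its conclusion, at whichever time point or contrast the plan designates; section 2.12 covers all time points and does not single out week 4.

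The cost is a few more imputation runs on data already collected, and a range of results to report in place of one number. No patients, visits or measurements are added. The article says that enrolment is under way, so the change can be recorded as an amendment before the data are analysed.
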